## Definitions

**Parasite clearance:** at least two consecutive negative smears for parasites obtained within an interval of 8 to 24 hours, post-dosing.

**Fever clearance:** at least two consecutive normal body temperature measurements obtained within an interval of 8 to 24 hours, post-dosing.

**Treatment failure:** the definition of treatment failure includes the following:

- ◆ Clinical deterioration due to *P. vivax* illness requiring hospitalization in presence of parasitaemia.
- ◆ Presence of parasitemia and axillary temperature  $\geq 37.5^{\circ}\text{C}$  any time between Day 3 and Day 28.
- ◆ Presence of parasitemia on any day between Day 7 and Day 28 irrespective of clinical condition.

**Cure on Day 14:** no parasitaemia on Day 14 irrespective of axillary temperature without previously meeting any of the criteria of treatment failure.

**Cure on Day 28:** no parasitaemia on Day 28 irrespective of axillary temperature without previously meeting any of the criteria of treatment failure.

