| Clinical and Laboratory Assessments | 
Baseline examination:
 
 
◆ Demographic data, medical history and history of medications.
 
◆ Physical examination, body weight and height, vital signs, and body temperature.
 
◆ Clinical signs and symptoms of malaria
 
◆ 12-lead ECG.
 
◆ Clinical safety laboratory evaluations: haematology, biochemistry and urinalysis (dipstick).
 
◆ Urine pregnancy test in female patients of child-bearing potential.
 
◆ Urine analysis for previous anti-malarial drugs, if feasible.
 
◆ Parasitological examination: thick and thin blood films for parasite species identification and count. Both asexual parasite and gametocyte counts will be recorded at screening.
 
◆ Screening for G-6-PD deficiency.
 
 
Routine assessments:
 
 
◆ Clinical 
 
○ Physical examination (on Days 0, 3, 28 and 42).
 
○ Recording of adverse events and concomitant medications.
 
○ Vital signs: on Days 0, 1, 2, 3, 7, 14, 21, 28, 35 and 42.
 
○ Body temperature: on Day 0 (Pre-dose) and every 8 hours for at least 72 hours or when fever has normalised (<37.5°C axillary/tympanic or <38.0°C oral/rectal): 2 normal readings taken between 8 and 24 hours apart. Also on Days 3, 7, 14, 21, 28, 35 and 42.
 
○ 12-lead ECG: on Day 0 (Pre-dose) and on Day 2, 2-4h post-dose and Day 28. Repeated, if clinically indicated, on Days 7, 14 and 42.
 
○ Clinical signs and symptoms of malaria on Day 0, 1, 2, 3 and any other day with fever.
 
 
 
◆ Laboratory tests: 
 
○ Haematology on Days 0, 3, 7, 28 and 42. Repeated if clinically indicated on other visits.
 
○ Blood biochemistry and urinalysis (by dipstick) on Days 0, 3, 7 and 28. Repeated if clinically indicated on Day 42.
 
○ Urine hCG test for pregnancy for female patients on Days 0, 14, 28 and 42.
 
 
 
◆ Parasitological examination: 
 
○ Thick and thin blood films for parasite count should be obtained and examined at screening on Day 0 to confirm inclusion/exclusion criteria. Thick blood films will be examined every 8 hours until at least 72 hours or until two consecutive negative readings are obtained not less than 8 and not more than 24 hours apart. Asexual parasite and gametocyte counts will both be recorded at screening, while total parasite counts will be recorded thereafter.
 
○ Thick blood films will be also examined on Days 3, 7, 14, 21, 28, 35 and 42 or on any other day if the patient spontaneously returns. Additionally, blood films should be obtained whenever parasitological reassessment is
 
 
 
 |

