|                                                  | 
required.
 
 
○ A thin blood smear will also be taken from Day 7 whenever parasitological blood samples are taken, and reserved in the event of recrudescence, to confirm Plasmodium species.
 
 
◆ PCR:
 
 
○ Samples will be taken for PCR prior to Day 0 dosing and immediately prior to Day 1 dosing. PCR filter paper samples will also be taken at Days 7, 14, 21, 28, 35 and 42. The PCR analysis will, however, only be performed in the case of positive microscopy for asexual parasites. This analysis will be centralized at the Swiss Tropical Institute in Basel.
 
                                                                                                                                                                                                                                                                                                                                             |
| Drug Blood Levels                                | 
At selected clinical study sites (as determined by the Sponsor), for each patient, two blood samples will be drawn for measurement of pyronaridine and two blood samples will be drawn for measurement of artesunate concentration. The blood samples will be taken at different timepoints within specific pre-defined time windows. The exact time of blood sampling must be recorded.
 
Additionally, at all sites, a blood sample must be drawn for assay of pyronaridine (in whole blood) at time of treatment failure.
                                                                                                                                                                                                                                                                                                                                                                                                                                                                                                 |

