### Artesunate

Artemisinin derivatives are powerful blood schizontocidal anti-malarial agents with a history of clinical use both alone and in combination with other drugs, mainly to treat *P. falciparum* malaria (Woodrow et al 2005), but also for *P. vivax* malaria (Li et al, 1994; Li et al 1999; Phan et al 2002).

The clinical efficacy of the artemisinin derivatives is characterised by an almost immediate onset and rapid reduction of parasitaemia, with complete clearance in most cases within 48 hours (De Vries et al, 1996). To prevent the recrudescence observed with monotherapy, however, treatment for at least 5 days is required.

Despite extensive clinical and laboratory experience, their molecular target is not yet fully identified.

Of the available derivatives, artesunate has the most favourable pharmacological profile for use in the treatment of uncomplicated malaria. The presence of a hemisuccinate group in the molecule confers water solubility and relatively high

oral bioavailability. It is rapidly and quantitatively converted *in vivo* to the potent active metabolite dihydro-artemisinin.

Studies of artesunate monotherapy for *P. vivax* infection have demonstrated rapid clearance of fever and parasites (Batty et al, 1998; Pukrittayakamee et al 2000; Hamed et al, 2004). Interestingly, a significant gametocidal activity of artesunate has also been reported. By reducing the transmission of *Plasmodium vivax* to the vector, artesunate could therefore reduce the incidence of *P. vivax* malaria (Nacher et al, 2004). However, 5-7 days monotherapy regimes are associated with recrudescence. This phenomenon highlights the limitations of monotherapy. To ensure high cure rates with short course 3-day therapy, combinations are recommended (Wilairatana et al, 1999; Tjitra et al, 2002; Silachamroon et al, 2003). Combination is also one method of overcoming drug-resistance and the use of combination antimalarial therapy, particularly artemisinin combination therapies (ACT), has been strongly recommended (WHO 2001).

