## 5. ASSESSMENTS

### 5.1. Efficacy Assessments

#### 5.1.1. Parasitological assessments

##### 5.1.1.1. Microscopy

Parasite density expressed as the number of parasites per microlitre ( $\mu\text{L}$ ) of blood will be measured serially to determine parasite clearance time (PCT). Asexual parasite and gametocyte counts will be recorded separately at screening, while total parasite counts will be recorded at any timepoint thereafter. Blood sampling for parasitology will be done usually by means of finger prick except when the timing for parasitology assessments coincide with time for clinical laboratory tests, in which cases, blood smears (thick and thin) and blood drop for PCR can be taken from the venous blood collected for clinical laboratory analyses.

Blood smears preparation, staining, examination and interpretation should be in accordance with the guidelines provided by the Sponsor. Any deviation from the Sponsor guidelines must be discussed and approved by the Sponsors before the study commences.

Thick and thin blood films for parasite count should be obtained and examined at screening on Day 0 to confirm inclusion/exclusion criteria. Thick blood films will be examined every 8 hours (+/- 1 hour) following first dose administration and for at least 72 hours (Day 1 and Day 2) or until the parasites have cleared as evidenced by two consecutive negative slide readings taken 8 to 24 hours apart. To avoid disruption of patient sleep at night, the first interval between the first dose administration and the next smear may be shorter or longer than 8 hours but shall not exceed 12 hours.

Thick blood films will be also examined on Days 3, 7, 14, 21, 28, 35 and 42 or on any other day if the patient spontaneously returns. Additionally, blood films should be obtained whenever parasitological reassessment is required. A thin blood smear will also be taken from Day 7 whenever parasitological blood samples are taken, and reserved in the event of recrudescence, to confirm *Plasmodium* species.

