|                                            | 
 
➤ Blood biochemistry and urinalysis
 
➤ Thick blood films (2) prepared 8-hourly
 
➤ Adverse events recording
 
➤ Concomitant medication recording
 
➤ Patient scheduled for follow up visits on Days 7, 14, 21, 28, 35 and 42
 
➤ Patient may be discharged from study site if parasite- and fever-free, with instructions to return in case of any recurrence of symptoms
 
 
note: If parasites and fever have not cleared on Day 3, the patient should be followed up until total clearance of parasites. If parasitaemia remains significant, the patient should be viewed as a treatment failure and withdrawn from the study. All End of Study Assessments (Day 28) should be performed before discharge and before rescue medication is given.
 
 
➤ Patient provided with an appropriate bed net
 
 |
| Assessment D7
(+/- 1 day)       | 
 
➤ Vital signs: BP and HR
 
➤ Temperature recorded
 
➤ Clinical signs and symptoms of malaria (if clinically indicated)
 
➤ 12-lead ECG (if clinically indicated)
 
➤ Haematology
 
➤ Blood biochemistry and urinalysis
 
➤ Thick blood films (2) for asexual parasites and gametocytes counts (the total count is recorded)
 
➤ Thin blood film (as a reserve)
 
➤ Sample for PCR (as a reserve)
 
➤ Adverse events recording
 
➤ Concomitant medication recording
 
                                                                                                                                                                                                                                                                                                                                                     |

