#### Primary Efficacy Endpoint

The primary efficacy endpoint for the study is the cure rate on Day 14.

Cure on Day 14 will be defined as no parasitemia on Day 14 irrespective of axillary temperature without previously meeting any of the criteria of treatment failure throughout the follow-up period.

Treatment failure is defined as any of the following:

- ◆ Clinical deterioration due to *P. vivax* illness requiring hospitalization in presence of parasitemia.
- ◆ Presence of parasitemia and axillary temperature  $\geq 37.5^{\circ}\text{C}$  any time between Day 3 and Day 28.
- ◆ Presence of parasitemia on any day between Day 7 and Day 28 irrespective of clinical condition.

Patients presenting a *P. falciparum* infection after clearance of *P. vivax* parasites should be treated accordingly and withdrawn. They should not be considered as *P. vivax* treatment failures.

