#### Secondary Efficacy Endpoints

The secondary efficacy endpoints are:

- Cure rate on Day 21 and Day 28, defined in the same way as cure rate on Day 14.
- Parasite Clearance Time (PCT).

Parasite clearance time is defined as the time from first dosing to time of first blood draw with parasite clearance. Parasite clearance

is defined as zero presence of asexual parasites for two consecutive negative readings taken between eight and twenty-four hours apart.

➤ **Fever Clearance Time (FCT)**

Fever clearance time is defined as the time from first dosing to first normal reading of temperature ( $<37.5^{\circ}\text{C}$  taken axillary or tympanic) for two consecutive normal temperature readings taken between eight and twenty-four hours apart.

The method of temperature measurement must be the same (i.e. axillary, tympanic, oral or rectal) for all measures in the same patient. Those patients who are initially included on history of fever and who do not subsequently have a documented temperature reading of over  $37.5^{\circ}\text{C}$  (taken axillary or tympanic) during the 24 hours following initial dosing, will not be included in this endpoint analysis.

- Proportion of patients who have cleared parasites on Day 1, 2 and 3
- Proportion of patients who have cleared fever on Day 1, 2 and 3

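### After screening only the total parasite count is recorded, although clearance is defined on asexual forms and cure and failure name no stage, so gametocyte-only slides cannot be told apart in the data

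*Protocol*

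**What the plan says.** **What is recorded.** Section 5.1.1.1 sets the rule: "Asexual parasite and gametocyte counts will be recorded separately at screening, while total parasite counts will be recorded at any timepoint thereafter". The Synopsis repeats it: "Asexual parasite and gametocyte counts will both be recorded at screening, while total parasite counts will be recorded thereafter". The visit schedule in section 6 applies it at Days 7, 14, 21, 28, 35 and 42 and at unscheduled visits, with entries of this kind: "Thick blood films (2) for asexual parasites and gametocytes counts (the total count is recorded".

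**What the endpoints need.**
- *Clearance, section 9.5.1.* For PCT, clearance "is defined as zero presence of asexual parasites for two consecutive negative readings taken between eight and twenty-four hours apart".
- *Clearance, Definitions page.* No stage is named: "at least two consecutive negative smears for parasites obtained within an interval of 8 to 24 hours, post-dosing".
- *Treatment failure* (Definitions, section 9.5.1, Attachment 3). One criterion is: "Presence of parasitemia on any day between Day 7 and Day 28 irrespective of clinical condition". Another combines parasitaemia with fever from Day 3. Neither names a stage.
- *Cure on Day 14, the primary endpoint.* It requires no parasitaemia on that day and no earlier failure, again without a stage.
- *PCR trigger.* In the Synopsis, PCR will "only be performed in the case of positive microscopy for asexual parasites". Section 5.1.1.2 triggers it on any positive slide when parasites reappear.

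Two further statements matter. Inclusion criterion 3b requires at least half of the entry density to be asexual, so gametocytes may make up the rest. The Introduction notes that "a significant gametocidal activity of artesunate has also been reported".

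**The concern.** The microscopist can tell the two forms apart, but from the first post-dose slide onward the record merges them. The endpoint definitions then either ask for the form that was not kept separately (PCT) or do not say which form counts (cure and failure).

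A statistical analysis plan can choose a definition of parasitaemia, but it cannot restore a count that was never written down. At stake are two secondary endpoints, PCT and the proportions cleared on Days 1 to 3. The Day 14 cure rate, on which the non-inferiority conclusion rests, is affected more indirectly. A patient scored as a failure also goes on to rescue medication under section 4.11, so the outcome without rescue cannot be observed afterwards.

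**Working it through.** **Step 1. Does the recorded count determine asexual clearance?** The recorded total is T = A + G (asexual plus gametocytes).
- T = 0 implies A = 0, so a zero total settles the matter.
- T > 0 leaves A unknown: it may be positive, or it may be zero with G > 0.

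Take the 8-hourly schedule and a patient whose recorded total is positive at 24 and 32 hours and zero at 40 and 48 hours, with asexual forms present up to 16 hours. The total count puts clearance at 40 hours. If the 24- and 32-hour slides held only gametocytes, section 9.5.1 puts it at 24 hours. The record is the same in both cases. So total-count PCT is at least as long as the defined PCT, and the proportion cleared on a given day is at most the defined proportion. The two agree unless gametocytes outlast asexual forms.

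**Step 2. Can this reach the primary endpoint?** Parasitaemia has no stated stage, and the only number recorded includes gametocytes. A slide with A = 0 and G > 0 from Day 7, or from Day 3 with fever, can therefore be scored as failure. Positive slides before Day 3 do not meet either of these criteria.

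**Step 3. The plan's own sample size (section 9.4), for scale.** Inputs: 90% cure in both arms, margin 10 points, two-sided 95% interval, 90% power, 205 evaluable per arm.
- Normal approximation: n = 2 × 0.9 × 0.1 × (1.960 + 1.282)² / 0.10² = 189.1, so 190 per arm.
- With continuity correction, n/4 × [1 + √(1 + 4/(0.10n))]² = 208.7, so 209 per arm, within 3% of the stated 205.
- Dropout: 410 / 0.9 = 455.6, so 456, as stated.
- Power at 205 per arm without correction: SE = √(2 × 0.09/205) = 0.0296; Φ(0.10/0.0296 − 1.960) = 92.1%.

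The sample size is not in question. It only supplies the denominator.

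**Step 4. Effect per patient.** 1/205 = 0.49 points in one arm. An excess of five patients in one arm would move the difference by 5/205 = 2.4 points, about a quarter of the margin. Five is an assumed figure.

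**Step 5. Illustration over an assumed range.** The documents give no rate of gametocyte-only slides. Assume that 0 to 5% of patients cured by an asexual definition are rescored as failures. At 90% cure and 205 per arm, 2% is 0.02 × 0.9 × 205 = 3.7 patients and 5% is 9.2 patients. All results use the uncorrected normal approximation.

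| Share rescored | Equal in both arms: power when true rates are 90% and 90% | Chloroquine arm only: apparent difference when true rates are PA 80%, chloroquine 90% | One-sided error in that case |
|---|---|---|---|
| 0% | 92.1% | −10.0 points | 2.5% |
| 2% | 88.1% | −8.2 points | 7.2% |
| 5% | 82.0% | −5.5 points | 22.6% |

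For example, 2% in chloroquine only gives 0.9 × 0.98 = 0.882 against 0.80, a difference of −8.2 points; SE = √((0.882 × 0.118 + 0.80 × 0.20)/205) = 0.0359; Φ((0.100 − 0.082)/0.0359 − 1.960) = 7.2%.

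**The case against.** The strongest reply is that the mismatch may rarely matter. A zero total does imply zero asexual parasites, so the stronger claim that PCT cannot be derived at all, which a reader might infer, is not supported: the total count gives the right answer except where gametocytes outlast asexual forms, and a bound otherwise. This stands.

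Nor does any section say that a gametocyte-only slide is a failure. That is a consequence of an undefined term. Section 5.1.1.1 refers smear interpretation to sponsor guidelines and the counting method, including gametocyte counts, to a laboratory manual that is not at hand. It also provides a third reader and a final classification by the site investigator when readings disagree, and blinded external reading of slides in suspected recrudescence. These steps may keep some such slides from being called failures. They do not close the gap, because no section provides for a stage-specific result to be recorded after screening.

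On PCR, the decision could be taken at the microscope without a recorded asexual count, and the PCR endpoints are exploratory. What remains is that the two statements of the trigger differ.

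A reader might also infer that the rule favours pyronaridine artesunate (PA), because artesunate is reported to be gametocidal and only one arm receives it. The documents do not support that as a finding. The Introduction gives no figure and no result for chloroquine, and nothing shows gametocytes persisting alone to Day 7. The half-of-density allowance at entry concerns Day 0 and says nothing about Day 7 or Day 14 slides.

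**Conclusion.** The recording rule and the endpoint definitions do not fit together. For PCT and the Day 1 to 3 clearance proportions, the data give bounds on the defined quantities rather than the quantities themselves whenever gametocytes persist longer than asexual forms. For the primary endpoint, a gametocyte-only slide can be scored as failure, and the recorded data would not let anyone check whether this had happened or in which arm.

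The size is unknown. The firm figure is 0.49 points of an arm's cure rate per reclassified patient, at 205 evaluable per arm. Equal misclassification in the two arms would cost power when the true cure rates are equal. An excess in the chloroquine arm would favour PA and raise the false non-inferiority rate. The 2% and 5% scenarios are assumptions that show sensitivity, not estimates. The case for correction rests on the inconsistency and on the loss of information, not on a demonstrated bias.

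**What to change.** 1. Record asexual and gametocyte counts separately on every post-dose slide, scheduled or not.
2. For the analysis endpoints, name the parasite stage in the definitions of clearance, cure, treatment failure and the PCR trigger, and make them agree across the Definitions page, the Synopsis, sections 5.1.1.2 and 9.5.1, and Attachment 3. Asexual *P. vivax* forms would match the existing PCT definition.
3. Report the total-count version of cure and clearance as a sensitivity analysis.
4. Keep this to endpoint definitions. Which slides lead to rescue treatment is for the sponsor to state, and that text should be reconciled with the endpoint wording.

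**Cost.** One extra CRF field per slide and a wording change; no extra slides. From Day 7 and at unscheduled visits the schedule already says that films are read for both forms. For the 8-hourly slides to 72 hours it does not, so separate counts there may be added work for the two readers.

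### Compliant film pairs can fail the parasite clearance definition: films may be 8 h ± 1 h apart, but two negatives count only if at least 8 h apart, so PCT and Day 1–3 clearance depend on how the rule is read

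*Protocol*

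**What the plan says.** Sampling. Section 5.1.1.1 (Microscopy) states "Thick blood films will be examined every 8 hours (+/- 1 hour) following first dose administration". The 72-hour sampling table in the same section gives nominal times of 0, 8, 16 and so on to 72 h. A relaxation for sleep covers only the interval from first dose to first film.

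Clearance rule. The sentence that sets the ± 1 h tolerance also lets films stop at "two consecutive negative slide readings taken 8 to 24 hours apart". The Synopsis makes the lower limit explicit: "two consecutive negative readings are obtained not less than 8 and not more than 24 hours apart". Section 9.5.1 carries the rule into the endpoint, where clearance "is defined as zero presence of asexual parasites for two consecutive negative readings taken between eight and twenty-four hours apart". The Definitions page is looser: "at least two consecutive negative smears for parasites obtained within an interval of 8 to 24 hours, post-dosing".

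Endpoint. Section 9.5.1: "Parasite clearance time is defined as the time from first dosing to time of first blood draw with parasite clearance". The proportions cleared of parasites on Days 1, 2 and 3 rest on the same notion of clearance. Section 9.5.2 censors patients without documented clearance beyond the longest observed clearance time.

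Fever. Section 9.5.1 uses "two consecutive normal temperature readings taken between eight and twenty-four hours apart". Section 5.1.2.1 schedules temperature every 8 hours and states no tolerance.

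Nowhere does the protocol give the 8 h minimum a tolerance or say that nominal times apply.

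**The concern.** The minimum gap for confirmation equals the nominal sampling gap, and only the sampling gap has slack. A film at 24 h 00 min and the next at 31 h 30 min are both on schedule. If both are negative, the two-reading rule on actual times still does not recognise clearance at 24 h; PCT moves to the next film that starts a pair at least 8 h apart. PCT and the Day 1–3 parasite proportions would then depend partly on minutes of clock time. Two analysts following different sections of the protocol could also report different PCTs from the same data.

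**Working it through.** The protocol gives no figure for the share of failing pairs, so there is none to reproduce.

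**Inputs.** From the protocol: nominal film times 8, 16, …, 72 h; tolerance ± 1 h; confirmation gap 8 to 24 h. Assumed: how actual times scatter within the window, and the distribution of true clearance times.

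**Permitted gaps.** The tolerance can be read in two ways.
- On each film: time = 8k + e(k) with |e| ≤ 1, so gap = 8 + e(k+1) − e(k), which lies between 6 and 10 h.
- On each gap: gap = 8 + e, which lies between 7 and 9 h.

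**Share of adjacent pairs under 8 h.**
- Per film: a pair is short when e(k+1) < e(k). For independent, identically distributed, continuous errors this has probability 1/2, whatever their skew. Simulation gives 50% for every continuous pattern tried.
- Per gap: 50% if errors are symmetric, 31% for a mildly late pattern, 0% if always late and 100% if always early.
- Recorded times rounded to 5 min: 45% per film, 43% per gap. Rounded to 15 min: 36% and 31%.
- Median shortfall is 10–35 min with continuous symmetric errors. The maximum is 120 min per film or 60 min per gap.

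**Effect on one patient, negative from the 24 h film on, adjacent pairs only (uniform errors).** PCT moves to a later film in 50% of patients (per film) or 48% (per gap). The mean delay is 5.3 h or 6.8 h among patients with a qualifying pair by 72 h. Six gaps remain from 24 to 72 h, so the chance that none qualifies is 1/7! = 0.02% per film, or (1/2)^6 = 1.6% per gap. The simulation agrees.

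**Effect on the endpoints.** True clearance is assumed lognormal with median 26 h and log SD 0.35. This puts observed PCT near the roughly 30 h that the Introduction reports for the phase II study in *P. falciparum*. Simulation: 200,000 patients, uniform ± 1 h error on each film.

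| | No minimum gap | Two readings, ≥ 8 h actual time | Run of three may qualify |
|---|---|---|---|
| Mean PCT (documented patients) | 31.5 h | 36.5 h | 31.3 h |
| Cleared by Day 1 film | 41% | 22% | 41% |
| Cleared by Day 2 film | 96% | 88% | 96% |

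The shift is 36.5 − 31.5 = 5.0 h, or 5.0/31.5 = 16%. About 52% of patients have PCT delayed or lost under the middle column. Results are nearly the same with errors of ± 15 or ± 30 min, so tighter timing does not help.

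**Hand check of Day 1.** Without a minimum: Φ(ln(24/26)/0.35) = Φ(−0.229) = 0.41. By 16 h the figure is Φ(ln(16/26)/0.35) = 0.083. So 0.410 − 0.083 = 0.327 of patients are first negative at 24 h, and about half of them have a qualifying next gap. Those already negative at 16 h qualify by the Day 1 film unless both following gaps are short (probability 1/3! = 1/6). The sum is 0.327 × 1/2 + 0.083 × 5/6 = 0.23, close to the simulated 22%. The small excess arises because a film that runs late is more likely to be the first negative, and the gap after it is then more often short.

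**Why a run of three removes the effect.** Three on-schedule films span 16 ± 2 h, that is 14 to 18 h, which always lies within 8 to 24 h.

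**The case against.** The strongest reply is that the harm depends on a reading the protocol does not force. The Definitions page allows more than two consecutive negatives, and three on-schedule films always fit the interval. A short pair does not release the site from 8-hourly sampling before 72 h, so the third film should normally exist. Use of nominal times would also make every permitted pair pass, and that choice could sit in a statistical analysis plan that is not shown. This stands as to size: on either reading the effect is close to nil. It does not remove the point. The Synopsis, 5.1.1.1 and 9.5.1 state a two-reading rule with an 8 h minimum, and none mentions runs or nominal times. The protocol itself fixes the endpoint, and its sections support answers about 5 h apart.

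Several stronger conclusions might be inferred but are not supported.
- *Bias between arms.* The trial is double-blind with one film schedule, and complete randomisation blocks go to each site, so timing habits fall on both arms alike. Day 14 cure does not use this definition.
- *Early sites fail and late sites pass.* This needs the tolerance to apply to each gap. If it applies to each film, a constant shift leaves the gaps unchanged.
- *Fever endpoints contradicted in the same way.* FCT and the Day 1–3 fever proportions have the same minimum with no slack, but no stated sampling tolerance. Only ordinary timing variation can make them fail.
- *Many patients never documented as clear.* The extra loss is small if films run to 72 h, and Section 6 continues 8-hourly films on Day 3, with follow-up until clearance if parasites and fever persist.
- *A material loss of log-rank power.* A rough check with assumed medians of 26 v 29 h and 205 per arm gave 74% falling to about 67%, from only 200 simulated trials. With 26 v 34 h there was no loss.

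**Conclusion.** The inconsistency is real and should be corrected. On the literal two-reading rule with actual times, about 30–50% of permitted adjacent film pairs fail. The 50% assumes exact times and no systematic early or late sampling; always-early or always-late gaps would give 100% or 0% if the tolerance is per gap. Under the assumed clearance distribution, mean PCT is inflated by about 5 h and the Day 1 proportion cleared is roughly halved. These sizes rest on that distribution and on independent timing errors, neither of which the protocol supplies. PCT and the Day 1–3 parasite proportions are affected directly; the two fever items share only the minimum without slack. The consequence is noise, inflated PCT and results that depend on the reading chosen. It affects secondary endpoints only.

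**What to change.** For the endpoint definitions, reconcile Definitions, the Synopsis, 5.1.1.1, 9.5.1 and the Attachment 2 footnotes (and 5.1.2.1 for temperature). Define clearance as negative (or normal) results at two consecutive scheduled readings, with a maximum of 24 h between them and one of:
- the 8 h minimum applied to nominal times; or
- the minimum on actual times lowered by the sampling tolerance: 8 − 1 − 1 = 6 h if ± 1 h applies to each film, or 8 − 1 = 7 h if it applies to each gap.

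State which meaning of ± 1 h is intended. PCT and FCT remain the time of the first of the two readings.

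Every permitted adjacent pair then qualifies, and the largest permitted adjacent gap (10 h or 9 h) stays well below 24 h. The cost is a wording change with no extra films. The small downside is that some pairs slightly under 8 h apart count as confirmation.
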